#### Secondary outcomes

The secondary outcomes (diet quality, eating competence, quality of life, work ability and functional capacity, cost-effectiveness) include the following:
Changes in the Index of Diet Quality (IDQ) [43, 44] from baseline to 12 monthsChanges in the Satter Eating Competence Inventory 2.0 (ecSI 2.0™) [45] and the Three-Factor Eating Questionnaire-R18 (TFEQ-R18) [46] from baseline to 12 monthsChanges in the Assessment of Quality of Life (AQoL-8D) [47] from baseline to 12 monthsChanges in the work ability and functional capacity questionnaire [48, 49] from baseline to 12 monthsThe difference in quality-adjusted life years (QALYs) between the intervention group and the control group.The incremental cost-effectiveness ratio (ICER) [50] as well as the incremental cost-utility ratio (ICUR) [50] of the intervention compared to the control group.

#### Follow-up outcomes

Follow-up outcomes are changes in the primary and secondary outcomes from baseline to the 8-week and 6-month follow-up.

Other pre-specified outcomes are as follows:
Treatment expectancy questionnaire: As treatment expectations may influence the outcome, they will be evaluated with the treatment expectancy questionnaire [51] and taken into account in the statistical analysis.Acceptability: The acceptability of the Food for Mind group rehabilitation program will be evaluated with the acceptability questionnaire based on the Theoretical Framework of Acceptability (TFA) [52].Changes in weight, body mass index (BMI), body fat, and fat-free body mass as measured with a body composition analyzer (InBody 720) from baseline to 12 months.

### Participant timeline {13}

Figure 1 shows the schematic diagram of study procedures.

### Sample size {14}

The total sample size of *n*=144 is based on the power calculation, when *α*=0.05, power=0.8, and effect size=0.5, and the estimated loss of participants is 15%. The calculation is based on the decline of 7 points assessed with the Center for Epidemiologic Studies Depression (CES-D) Scale.

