#### Intervention description {11a}

Both the FM intervention groups and the BGM control (befriending) groups meet 6 times (5 1.5-h sessions and 1 3-h session) over an 8-week period. Each group has 6 to 8 participants. For social peer support, both groups will have their own WhatsApp groups, in which participants can share their own experiences and findings. The WhatsApp mobile application is used during the intervention and for the subsequent 10 months. Both groups continue their usual treatment for depression (treatment as usual) during the study.

A written manuscript prepared for every FM group meeting drawn up together in collaboration with a behavioral scientist helps the research dietitian to stick to a cohesive plan when instructing the group. The implementation of the BGM group meetings is also harmonized by the same instructor.

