## Statistical methods

### Statistical methods for primary and secondary outcomes {20a}

The effects of the intervention on the primary and secondary outcomes will be analyzed following the intention-to-treat (ITT) principle. Group differences will be estimated using linear mixed effects models which allow considering the nested dependency structure generated from small groups and small group counselors in the data. All tests will be conducted using an alpha level of 0.05 and reporting 95% confidence intervals. Statistical analysis will be performed using the R software [72] and IBM SPSS Statistics® (IBM Corp., Armonk, NY, USA).

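### The stated 80% power allows nothing for correlation within the small groups, which the planned analysis does model

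*Protocol article*

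**What the plan says.** Sample size {14} states: "The total sample size of *n*=144 is based on the power calculation", with alpha 0.05 and "power=0.8, and effect size=0.5, and the estimated loss of participants is 15" per cent. It adds: "The calculation is based on the decline of 7 points assessed with the Center for Epidemiologic Studies Depression (CES-D) Scale". It gives no ICC, design effect, group size or standard deviation.

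Intervention description {11a} has both arms meeting six times over 8 weeks in small groups: "Each group has 6 to 8 participants". Sequence generation {16a} randomises individuals in blocks of 12 to 16, each block filling one intervention group and one control group.

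Statistical methods {20a} will estimate group differences with "linear mixed effects models which allow considering the nested dependency structure generated from small groups and small group counselors in the data", and adds: "All tests will be conducted using an alpha level of 0.05 and reporting 95% confidence intervals". The primary outcome (Outcomes {12}) is change in CES-D from baseline to 12 months.

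**The concern.** Two current sections treat the same data differently. The analysis section expects outcomes within a small group to be correlated and builds that into the model. The sample size section counts every participant as independent. Shared group experience is part of both treatments: Table 1 names giving and receiving social support as an aim of the nutrition meetings, and the control arm is itself a social support group.

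If outcomes are positively correlated within groups, the treatment contrast has a larger standard error than the sample size calculation assumes, and it rests on 9 to 12 groups per arm. A reader who met a null 12-month result would then judge it against an 80% chance of detecting 7 points that this design may not have.

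**Working it through.** **Inputs from the article.** 72 per arm; alpha 0.05; power 0.80; standardised effect 0.5; 7 CES-D points; 15% loss; groups of 6 to 8, hence 72/8 = 9 to 72/6 = 12 groups per arm. The sample size section does not state sidedness. Two-sided is taken from the 95% intervals; a one-sided test needs 50 per arm, and 100 x 1.15 = 115 is far from 144.

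**Inputs assumed.** ICC from 0 to 0.10, the same in both arms, and no gain from baseline adjustment. The SD is implied: 7/0.5 = 14.

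**Step 1: reproduce 144.**
- n per arm = 2(1.960 + 0.842)²/0.5² = 62.8, so 63 per arm and 126 in total.
- 126 x 1.15 = 144.9, within one or two of 144.
- The t-test version needs 64 per arm: 128 x 1.15 = 147.
- Dividing by 0.85 instead gives 126/0.85 = 148 or 128/0.85 = 151.

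The match is approximate. The nearest route uses independent observations and a loss allowance, and nothing is left over for clustering.

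**Step 2: power with no clustering.** 72 x 0.85 = 61.2 per arm analysed. Power is 79% (normal approximation) or 78% (t). The gap from 80% arises because 144 x 0.85 = 122.4 is below the 126 required. That is a separate and smaller matter.

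**Step 3: add the small groups.** Analysed group size m = 61.2/12 = 5.1 to 61.2/9 = 6.8. Design effect DE = 1 + (m - 1) x ICC. Effective n per arm = 61.2/DE. Power comes from the noncentral t with noncentrality 0.5 x sqrt(effective n/2), on 120 degrees of freedom and then on 2(k - 1) = 16 to 22 for k = 9 to 12 groups per arm.

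| ICC (assumed) | DE | Effective n per arm | Power, df 120 | Power, df 16-22 |
|---|---|---|---|---|
| 0 | 1.00 | 61.2 | 78% | 74-75% |
| 0.01 | 1.04-1.06 | 57.8-58.8 | 76-77% | 71-74% |
| 0.02 | 1.08-1.12 | 54.8-56.6 | 74-75% | 69-72% |
| 0.05 | 1.21-1.29 | 47.4-50.8 | 68-71% | 63-67% |
| 0.10 | 1.41-1.58 | 38.7-43.4 | 59-64% | 54-61% |

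With no loss at all (72 per arm, 85% at ICC 0), the normal approximation stays at or above 80% only up to an ICC of about 0.02 (groups of 8) to 0.03 (groups of 6).

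**Step 4: detectable difference at ICC 0.05, 80% power, SD 14.**
- Normal approximation: 2.802 x 14 x sqrt(2/50.8) = 7.8 points to 2.802 x 14 x sqrt(2/47.4) = 8.1 points.
- Group-level df: (2.074 + 0.858) x 14 x sqrt(2/50.8) = 8.1 points (df 22) to (2.120 + 0.865) x 14 x sqrt(2/47.4) = 8.6 points (df 16).

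These figures cover the small-group level only, not the counselor level that the model also names.

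**The case against.** **The ICC is not in the article.** The sessions end at 8 weeks and the endpoint is at 12 months, so correlation may have faded. WhatsApp contact was planned for the ten months after the sessions, but the Discussion says its role must be re-evaluated. At ICC 0 power is 78%, close to the claim. This objection stands. It limits any statement of size, but not the observation that nothing was allowed for clustering.

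**The model may recover precision.** If 14 is a raw-score SD and the baseline correlation is 0.5 (an assumption), baseline adjustment multiplies the variance by 1 - 0.5² = 0.75. With df 120, power is then about 80-82% at ICC 0.05 and 71-76% at ICC 0.10. At correlation 0.3 and ICC 0.05 it is about 72-75%. A plain change score at correlation 0.5 gains nothing, since 2 x 14² x (1 - 0.5) = 14². This also stands as a possibility. The sample size section claims no such gain and does not say which SD it uses, so the gain cannot be credited to the stated 80%.

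**The group-level df figures are not purely a clustering effect.** They give 74-75% even at ICC 0, and the article fixes no df method. They are the cautious end.

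**Stronger readings a reader might infer.** One is that the trial is known to have only 59% power; that rests on an ICC the article does not give. Another is that the analysis ignores clustering or that its intervals are invalid. Statistical methods {20a} includes the small groups in the model, so the reported interval is meant to carry the clustering whatever was planned. A third is that more participants are needed; with ICC and baseline gain both unknown, the article does not establish that.

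**Conclusion.** The concern holds as a mis-stated power. The 144 is accounted for by an independent-observations calculation plus the loss allowance, while the same article delivers both arms in small groups and models dependency within them. For any positive ICC the 80% is not a property of this design unless an unstated baseline or repeated-measures gain offsets it.

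The direction is firm and the size is conditional. Across assumed ICCs of 0.01 to 0.10 the shortfall from 80% runs from about 3 to about 21 points on 120 degrees of freedom. At ICC 0.05 the difference detectable with 80% power is about 8 points, against the 7 planned. Both rest on 61.2 analysed per arm, 9 to 12 groups per arm, an implied SD of 14 and no baseline gain. Should-fix.

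**What to change.** Keep 144 and rewrite Sample size {14} so that it:
- gives power for groups of 6 to 8 over an ICC range that includes 0, with the basis for the range;
- labels the SD of 14 as implied by 7/0.5 and says whether it is a raw-score or a change-score SD;
- states any baseline or repeated-measures gain relied on, with the correlation assumed;
- states the degrees-of-freedom method.

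Possible wording: with 144 randomised, 15% loss, groups of 6 to 8, an implied SD of 14 and no baseline gain, power for a 7-point difference is about 78% at ICC 0, 76-77% at 0.01, 74-75% at 0.02, 68-71% at 0.05 and 59-64% at 0.10, and 3 to 5 points lower with group-level degrees of freedom.

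Add that a null 12-month result will be interpreted from its confidence interval and not against the 80% figure. The change is one paragraph, with no extra participants and no change to the analysis model. Its only cost is a less favourable stated power.

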## Trial design {8}

This study is a two-parallel group, randomized controlled clinical trial exploring the effects of a strength-based nutrition group intervention in patients diagnosed with depression. In this trial with a subject allocation ratio of 1:1, the Food for Mind intervention is expected to be superior to a social support group as a standalone intervention. The protocol is outlined in Fig. 1, and details of the assessments are given in Table 2.

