### Assignment of interventions: allocation

#### Sequence generation {16a}

Participants will be randomized either into the FM behavioral nutrition intervention group (*n*=72) or the BGM control (befriending) group (*n*=72) in a 50:50 ratio using block randomization, which is a commonly used technique in clinical trial design [53].

Each pair of the starting intervention and control small groups (*n*=12–16) will form one block. A random study number between 1000 and 9999, and a number coding the treatment (0 = control, 1 = intervention) will be generated with Microsoft Excel for each study participant. Treatment numbers will be generated in a way that ensures that the setup becomes balanced.

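### n=144 does not keep 80% power at the stated 15% loss: the loss appears to have been added (× 1.15) instead of divided out (÷ 0.85)

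*Protocol article*

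**What the plan says.** In the protocol article, Sample size {14} sets the total at 144, with α=0.05 and "power=0.8, and effect size=0.5, and the estimated loss of participants is 15" per cent. It adds that "The calculation is based on the decline of 7 points" on the CES-D. Trial design {8} fixes a "subject allocation ratio of 1:1", and Sequence generation {16a} gives 72 per arm, which agrees with 144.

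The section does not say whether the test is one- or two-sided, whether a normal or a t-based formula was used, or how the 15% was applied. The statistical methods section {20a} repeats the 0.05 level and plans on "reporting 95% confidence intervals", which points to two-sided testing.

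**The concern.** A reader takes the sentence to mean that 80% power for a standardised effect of 0.5 remains after 15% of participants are lost. The inputs needed to check this, apart from the sidedness and the formula, stand in the same sentence, and under either usual formula the statement is not quite true. Loss is normally a share of those randomised, so the number to randomise is the evaluable number divided by 0.85. The stated total looks like the evaluable number multiplied by 1.15, which is always smaller.

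At stake is the accuracy of the article's sample-size justification: either the power or the tolerated loss is slightly overstated.

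**Working it through.** **Inputs.** α = 0.05 (Sample size {14}; repeated in {20a}). Two-sided is an assumption, in line with the 95% confidence intervals. Power 0.80, standardised effect d = 0.5 and loss 15% are from Sample size {14}. Allocation is 1:1, with 72 per arm, from {8} and {16a}. The SD is not stated; 7 points at d = 0.5 implies 7/0.5 = 14.

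**Evaluable participants needed per arm.**
- Normal approximation: 2 × ((1.960 + 0.842)/0.5)² = 62.79, so 63 per arm, 126 in total.
- Two-sample t-test, solved exactly: 63.77, so 64 per arm, 128 in total.

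**Reproducing 144.** 63 × 1.15 = 72.45, rounded down to 72 per arm, or 144 in total. Without rounding first, 2 × 62.79 × 1.15 = 144.4. This matches both the total and the 72 per arm. Rounding up, as is usual, would have given 145 (from 126 × 1.15 = 144.9) or 146 (73 per arm).

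**Why × 1.15 falls short.** Losing 15% of an additively inflated sample leaves 1.15 × 0.85 = 0.9775 of the requirement, not all of it.

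**Inflating by division.**

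| Formula | Calculation | Total to randomise |
|---|---|---|
| Normal, unrounded | 2 × 62.79 / 0.85 = 147.7 | 148 |
| Normal, from 126 | 126 / 0.85 = 148.2 | 149 |
| Normal, rounded up per arm | 63 / 0.85 = 74.1, so 75 | 150 |
| t-test, from 128 | 128 / 0.85 = 150.6 | 151 |
| t-test, rounded up per arm | 64 / 0.85 = 75.3, so 76 | 152 |

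Every version exceeds 144, by 4 to 8.

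**What 144 delivers at 15% loss.** 144 × 0.85 = 122.4, or 61.2 per arm, below both 63 and 64.
- Power at 61 per arm: 78.2% (t-test), 78.9% (normal).
- Power at 61.2 per arm: 78.3% (t-test), 79.0% (normal).
- Effect detectable with 80% power at 61.2 per arm (t-test): d = 0.511. With the implied SD of 14 that is about 7.1 CES-D points, against the planned 7.

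**Loss that 144 can absorb at 80% power.** t-test: 1 − 128/144 = 11.1%. Normal: 1 − 126/144 = 12.5%.

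**One-sided testing as an explanation.** The normal approximation gives 50 per arm, 100 in total: 115 after × 1.15 and 118 after ÷ 0.85. Neither is near 144, so sidedness does not account for the figure.

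**The case against.** The best defence is that 144 follows from the stated inputs by a simple route, 63 × 1.15, and that the article does not commit itself to a t-test or to a way of applying the loss. This stands. A reader who tries only the t-test, or only division by 0.85, might infer that 144 cannot be derived at all. That is not supported: the normal approximation with additive inflation returns both the total and the per-arm number. Nor is 151 to 152 the only corrected answer; under the normal approximation it is 148 to 150.

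One could also read the 15% as a share of the evaluable number, which would make × 1.15 deliberate. But loss of participants is ordinarily counted from those randomised. Even on the other reading, the rounding went down from 72.45, and 144 covers only 12.5% of those randomised.

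The second defence is size. One to two points of power is less than the uncertainty in the assumed effect and in the loss rate. This also stands, and it settles the severity. It does not make the sentence correct.

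A reader might add that the trial plans for nesting in small groups, so that the gap matters more. Whether the size allows for clustering is a separate question and lends this point no weight.

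**Conclusion.** The point holds and is minor. The stated combination of 144 participants, d = 0.5, 80% power and 15% loss is not met under either usual formula. At 15% loss, power is about 78% to 79%; for 80%, loss must stay at or below about 11% (t-test) or 12.5% (normal). The shortfall is 4 to 8 participants, or 1 to 2 points of power.

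Additive inflation is an inference from the exact match with 63 × 1.15, not something the article states. The power and loss figures do not depend on that inference. They rest on a two-sided 0.05 test, a simple comparison of two means, equal loss in both arms and no adjustment for clustering.

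The figures do not support the stronger inference that the trial is materially underpowered for this reason or should enrol more participants.

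**What to change.** Restate Sample size {14} so that its numbers agree, and name the formula and the two-sided level. Either of these would do:
- *n=144 with 15% loss gives about 78–79% power for d=0.5 (two-sided α=0.05).*
- *n=144 gives 80% power for d=0.5 (two-sided α=0.05) if loss does not exceed about 11–12.5%.*

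Once the formula is named, the range narrows to one figure: 78% or 11% for the t-test, 79% or 12.5% for the normal approximation. Either sentence should say that it is before any allowance for clustering.

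The cost is one sentence and a slightly less favourable figure. Enrolment, conduct and analysis do not change.

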### Recruitment {15}

Recruitment will be conducted in collaboration with ten public and private health care service providers (public health and occupational health care) in Northern Savo, near the University of Eastern Finland’s Kuopio Campus. The principal investigator and the research dietitian will introduce the study to the health care staff (doctors, nurses, psychologists) as part of their clinical team meetings in all recruiting organizations and will distribute tailored brochures targeted separately at health care staff and patients. The staff are also given a suggestion of how to introduce the study to potentially eligible patients. These instructions were developed by the behavioral scientist and the principal investigator of the research team.

The staff will select potentially eligible patients according to the diagnostic criteria, introduce the study to the patients with the material described above, and inquire them about their willingness and readiness for participation. Based on the participants’ consent, their contact information is provided to the research dietitian for further eligibility screening.

The visibility of the study will also be increased by placing posters with general information about the study on notice boards for the purpose of collaborative recruitment at health care units, public libraries, and cafes and by publishing Facebook ads and sending emails in co-operation with local associations. Information about the study is also available online (www.ruokaamielelle.fi) and on a social media platform (Facebook).

### Assignment of interventions: allocation

#### Sequence generation {16a}

Participants will be randomized either into the FM behavioral nutrition intervention group (*n*=72) or the BGM control (befriending) group (*n*=72) in a 50:50 ratio using block randomization, which is a commonly used technique in clinical trial design [53].

Each pair of the starting intervention and control small groups (*n*=12–16) will form one block. A random study number between 1000 and 9999, and a number coding the treatment (0 = control, 1 = intervention) will be generated with Microsoft Excel for each study participant. Treatment numbers will be generated in a way that ensures that the setup becomes balanced.

#### Concealment mechanism {16b}

To prevent forehand knowledge of the allocation sequence, randomization is done separately for each block (*n*=12–16) after obtaining the participants’ consent and conducting baseline assessments. With this procedure, the aim is to ensure that prior information does not selectively influence the choice of subjects.

#### Implementation {16c}

The research dietitian will register eligible participants after obtaining consent at a face-to-face meeting. A data manager not connected to the study will perform the randomization and send the random numbers and group assignment directly to the research dietitian by email, who provides information about the allocation results to the participants by SMS and email including the meeting schedule and group program. If a person is unwilling to participate in the BGM control group after being randomized into it, she/he will be encouraged to participate by the research dietitian, highlighting that all participants in the BGM group will have an opportunity to participate in one Food for Mind nutrition meeting and receive the Food for Mind counseling material at the end of the study. Naturally, there is an option to refuse to participate in the study.

### Assignment of interventions: blinding

#### Who will be blinded {17a}

Due to the limitations in research resources, we will not be able to blind the care providers or outcome assessors. This is unlikely to introduce bias as the main outcome measure is the self-administered questionnaires, filled out by the participants. To avoid confirmation bias, participants’ data will be re-coded for statistical analysis by a data manager not related to the study, or if possible, the data will be analyzed by an external data analyst.

#### Procedure for unblinding if needed {17b}

An open-label design is used to avoid unblinding.

## Data collection and management

### Plans for assessment and collection of outcomes {18a}

The questionnaires and methods used for the assessments are presented in Table 2. Self-administered AQoL-8D and treatment expectancy questionnaires have been double-translated from English into Finnish.

**Table 2 Tab2:** Assessment time points

Questionnaire/method	0	8weeks	6months	12months
Baseline characteristics				
Age, sex, education, occupation, working time pattern, marital status, household size, smoking, alcohol use, special diet	x			
Diagnosis of depression, year of first diagnosis	x	x	x	x
Medication	x	x	x	x
Employment status	x		x	x
Distance to group meeting facilities, mode of transportation	x			
Depression				
Center for Epidemiologic Studies Depression (CES-D) Scale	x	x	x	x
Seasonal Pattern Assessment Questionnaire (SPAQ)	x			
Quality of diet				
The Index of Diet Quality (IDQ)	x	x	x	x
Diet Frequency Questionnaire	x	x	x	x
Household management questionnaire	x	x	x	x
Eating behavior				
*Three-Factor Eating Questionnaire-r18* (TFEQ-r18)	x	x	x	x
Satter Eating Competence Inventory (ecSI 2.0™)	x	x	x	x
Quality of life				
Assessment of Quality of Life (AQoL-8D)	x	x	x	x
Ability to work and function				
Ability to work and function questionnaire	x	x	x	x
Cost-effectiveness				
Distance and mode of transportation to group meetings	x			
Costs of intervention				x
Costs of participants’ time use				x
Cost of participants’ travel				x
Treatment expectancy				
Treatment expectancy questionnaire	x			
Acceptability				
Theoretical Framework of Acceptability (TFA)		x		
Weight and body composition				
Body composition analyzer (InBody720)	x	x	x	x

